### Intervention

The WHO PSS-SRH draft intervention package consists of eight modules/sessions focused on SRH education, psychoeducation, and enhancing skills acquisition (specifically around: emotional regulation, communication, problem management, decision-making, and self-efficacy). It is designed to be delivered by trained community paraprofessionals (non-specialists) with at least twelve years of formal education. The draft intervention package will be administered (at the selected PHCs) once a week (for each subgroup) for a duration of 90 min over a total of 8 consecutive weeks. To create a supportive and collaborative environment for the participants in the study, each LWC member will be assigned to an EG subgroup and will attend all their sessions. The involvement of LWC members is expected to build trust and ensure a culturally sensitive approach throughout the intervention delivery. This will play a crucial role in fostering a sense of community among participants, encouraging open discussions, and facilitating the sharing of experiences and ideas. A midwife and a clinical psychologist will also attend all sessions of the intervention to support the paraprofessional when/if needed and to ensure protocol adherence as well as quality and content fidelity. Importantly, the psychologist and midwife will also support participants during the session should they feel distressed, especially when discussing sensitive topics. In such an event, the psychologist or midwife would first attend to the concerns of the participant separately, and if the need arises, they may refer them to relevant care services from professionals within the given PHC or to specialised care outside of the PHC. The intervention delivery schematic (which includes personnel, location, and days of intervention delivery) is displayed in Figure 2.

**Figure 2 F2:**
[figure not shown]
Intervention package delivery schematic diagram.

### Facilitator selection and training

A team of women paraprofessionals (non-specialists), from the target population, will be responsible for implementing the intervention package. The paraprofessionals will be selected, with the help of the PHCs, LWC, and CC, based on the criterion of having a minimum of 12 years of formal education. These paraprofessionals will receive a twenty-day comprehensive training facilitated by a clinical psychologist and a SRH expert, both of whom have experience working with Syrian refugee populations. The training will equip them with the necessary skills and knowledge to effectively deliver the intervention content in a standardized manner and address any concerns or questions that may arise during the sessions. The training will cover a range of topics, including ethical training, session implementation, role playing, and strategies for managing challenging scenarios. To ensure their readiness to implement the intervention, the paraprofessionals performance will be assessed by the team during the training, who will also select the top performing paraprofessionals to participate in the intervention delivery.

### Ethical approval

This RCT has received ethical approval from the Institutional Review Board (IRB) at the American University of Beirut (AUB) (SBS-2023-0119 and SBS-2023-0310) and from World Health Organization (WHO) Research Project Review Panel (RP2) (A66058.5865) and Ethical Review Committee (ERC), both of which are in accordance with the Declaration of Helsinki.

### Blinding

A single-blinded design was chosen because study participants will be aware of whether they are in the experimental or control group, since they would either receive or not receive the intervention package. The team collecting the data on the other hand will not be aware of which participants are in the control and which are in the experimental groups, since post-intervention questionnaires do not inquire about participants' receipt of the intervention. Additionally, data collectors will be explicitly instructed not to inquire about this information when in contact with participants.

### Contamination

Contamination risks are considered minimal in this intervention. Primarily, this is because the sessions will focus on skill building and is largely participatory through in-class group discussions. This means that it is unlikely for learnings to be transmitted to others who are not part of the experimental group. Participants will also be asked not to share any information about the intervention with others to maintain confidentiality and privacy of the group. They will also be asked not to share material or knowledge with others until the end of the study period. Because contamination risks were deemed minimal as this intervention focuses on skill building and is highly participatory, potential contamination will not be formally measured. This may present a limitation that should be considered when interpreting findings.

### Outcome measures

To thoroughly evaluate the impact and effectiveness of the intervention package, we will employ a comprehensive set of questionnaires (incorporating various tools) that will be administered to both the EG and CG. These questionnaires will enable the research team to thoroughly assess the impact of the intervention package on various aspects of the participants' lives, including their well-being and SRH. Refer to Table 1 for a detailed description of each tool and the time of administration.

**Table 1 T1:** Outcome evaluation tools and time of administration.

Outcome	Aim	Tool	Study period			
			Screening	Baseline T0	End-line T1 (8 weeks)	3 months post-intervention T2 (20 weeks)
Participant Inclusion	Inclusion and exclusion	Screening tool (24 questions)	X			
Primary outcome	At least 20% improvement in family planning use among the EG compared to the CG at three months.	Pan Arab-Family Health (PAPFAM) survey (24) (BL: 68 questions; EL: 35 questions; P3M: 37 questions)		X	X	X
Secondary outcomes	Improved well-being among the EG compared to the CG at three months. Multiple dimensions of well-being will be assessed.	Hopkins Symptom Checklist 25 (25 questions) (20, 25, 26)		X	X	X
		WHO-5 Wellbeing (5 questions) (27)		X	X	X
		General Self-Efficacy Scale (10 questions) (28)		X	X	X
		Multidimensional Scale of Perceived Social Support for Arab Women (12 questions) (29)		X	X	X
Intermediate outcomes	Improvement in important mediators in the EG compared to the CG	The Difficulties in Emotion Regulation Scale Short Form DERS-SF (18 question) (30, 31)		X	X	X
		Interpersonal Communication Competency scale (32) (17 question)		X	X	X
		Revised Ways of Coping Checklist (12 questions) (33)		X	X	X
Important variables and confounder	Such as socio-demographic factors; Family planning including other SRH knowledge; Women's reproductive and obstetric history; Gender disadvantage; and previous history of domestic violence	Using questions from the PAPFAM Survey (24).		X	X	X

Outcome evaluation will be conducted at baseline (T0) followed by the implementation of the intervention. The end-line outcome evaluation (T1) will be conducted on the final session (8th session) of the intervention. Subsequently, the post-3 months outcome evaluation (T2) will be conducted 3 months after T1. In cases where the participants do not attend a scheduled assessment (T1 or T2), three attempts will be made in the same week, followed by one in the subsequent week to schedule a new appointment via telephone.

The majority of the tools have been used and validated in Arabic in various settings. One of the tools, Interpersonal Competency Scale (ICCS) was not available in Arabic and was therefore translated into simple, colloquial Arabic that can be understood by participants (i.e., low literacy participants) following recommended procedures for cross-cultural research. Translation followed the WHO Guidelines on Translation. The steps included: forward translation to Arabic by a translator (who is a bilingual, native Arabic speaker) with a psychological/health background. Next, an expert panel, which consists of 2–3 bilingual experts in the field, was held to identify and resolve the inadequate expressions/concepts of the translation, as well as any discrepancies between the forward translation and the original document. After that, the back translation to English was be done by a translator who is also a bilingual, native English speaker. The last step will was pre-testing the translated version with a population similar to the target population (15–24 year old female Syrian refugees). This stage included cognitive interviews asking the participants what they think of each translated component, which was done through interviews.

Outcome evaluation instruments will be administered through a single questionnaire, in person, on a tablet using an electronic data collection software, KoBo. All data collected through KoBo will be stored on password-protected tablets and secured on institutional servers the American University of Beirut. Access to study data will be authorised only to members of the research team with password protected accounts. Data shared with study statistician will be anonymised and participants will be identified by codes without any personal information assigned to them. Should adverse events be identified during data collection, management, or analysis, the protocol states that they be immediately directed towards the study's principle investigator to determine the appropriate course of action. The study will employ female data collectors as some women may feel more at ease in discussing sensitive topics related to SRH with individuals of the same gender. Prior to their enrolment in the study, the data collectors will receive a training on various aspects, including the different sections of the questionnaires, research ethics, risk of bias in collecting data, reporting procedures of adverse events, data management, managing distress, obtaining informed consent, as well as referral mechanisms. The training, which will span over two days, will provide the data collectors the opportunity to engage in role-playing to ensure proper data collection methods.

To ensure that the research questionnaire is easy to understand and accurately captures the necessary data, a pilot will be conducted with a group of Syrian refugees similar to the target population before the actual initiation of the RCT. The purpose of the pilot test is to identify survey issues such as unclear wording or confusing questions or the length of the outcome evaluation questionnaire. Feedback collected from the pilot test will be used to refine the questionnaire for use in the actual RCT.

#### Primary outcome

The primary outcome of the intervention is to improve contraception/family planning use among the EG compared to the CG at 3 months. This will be measured by the Pan Arab-Family Health (PAPFAM) survey (34). The PAPFAM survey is similar to the well-known Demographic and Health Survey in design but with a focus on family health in the Arab countries. It uses a standardized instrument to collect data mainly on maternal health and reproductive health of women as well as data on child, adolescent, and elderly health. The study will use only relevant sections of the PAPFAM survey, chosen based on their alignment with the study's objectives and research questions. Specifically, questions that assess participants' knowledge, attitudes, and practices related to family planning methods, and utilization of family planning services have been extracted. Other questions relating to socio-economic status, marriage, and STI knowledge have also been extracted.

#### Secondary outcomes

The secondary objective of the intervention is to improve mental well-being among the EG compared to the CG at 3 months. To measure the improvement in mental well-being, changes in common mental distress, quality of life, self-efficacy, and social support will be assessed.

Common mental distress will be measured by the Hopkins Symptoms Checklist-25 (HSCL-25) (20). The HSCL-25 will be used to measure the participants' level of depression, anxiety, and stress.

Quality of life will be measured by the World Health Organization Well-Being 5-item Index (WHO-5) (27). The WHO-5 is a short 5-item instrument that measures psychological well-being, including depression. Each of the 5 positively worded items is rated on a 6-point Likert scale ranging from 0 (constantly present or all the time) to 5 (not present or at no time). The summed scores range from 0 to 25. A score <13 indicates poor wellbeing or low mood, though not necessarily depression and warrants further assessment (35).

Self-efficacy will be measured using the General Self-Efficacy Scale (GSES) (28). It is a 10-items scale designed to assess a person's optimistic self-beliefs used to cope with life's demands.

Social support will be measured by the Multidimensional Scale of Perceived Social Support for Arab Women (MSPSS-AW) (29). The 12- Item tool will assess the participants' perceptions of the availability and quality of emotional, instrumental, and informational support from friends, family, and community members.

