Analysis of secondary outcomes will be conducted at endline (T1) and 3 months post-intervention (T2) 1- to evaluate the potential increase in the secondary outcomes (well-being), and 2- in the use of the other SRH services associated with the intervention; 3- to investigate potential mediators of the primary comparison; 4- to investigate the effect of co-interventions and adherence. Mediators will be assessed as additional explanatory variables to the primary logistic regression models.

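### The WHO-5 response anchors run opposite to the cut-off given in the same paragraph, and no reverse-scoring step reconciles them

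*Protocol article*

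**What the plan says.** All the scoring information is in one paragraph of the protocol article, under Outcome measures, Secondary outcomes. It makes four statements about the WHO-5:

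- Item wording: "Each of the 5 positively worded items is rated on a 6-point Likert scale".
- Anchors: "ranging from 0 (constantly present or all the time) to 5 (not present or at no time".
- Total: "The summed scores range from 0 to 25".
- Interpretation: "A score <13 indicates poor wellbeing or low mood, though not necessarily depression and warrants further assessment".

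The instrument's role is given just before: "Quality of life will be measured by the World Health Organization Well-Being 5-item Index (WHO-5". It is one of four well-being measures under the secondary objective, with the HSCL-25, the General Self-Efficacy Scale and the social support scale. Table 1 schedules it at T0, T1 and T2. Neither this paragraph nor the Analysis section mentions reverse scoring, and no sentence says outright whether a higher WHO-5 total is better or worse.

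**The concern.** The anchors and the cut-off imply opposite directions for the same total. For a positively worded item, an anchor of 0 for constant presence gives the lowest score to the woman who is doing best. A cut-off that labels low totals as poor well-being gives the lowest score to the woman who is doing worst. An analyst who builds the score from the anchors and reads it by the cut-off gets the direction wrong.

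At stake is the sign of the treatment effect on the trial's only named quality-of-life measure. The objective is directional: "The secondary objective of the intervention is to improve mental well-being among the EG compared to the CG at 3 months". A true gain could be reported as a loss, or a true loss as a gain. The scales in this trial do not all run one way (the article says that higher DERS-SF scores mean more difficulty), so an analyst cannot assume a common direction.

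**Working it through.** **Inputs**, all from the WHO-5 paragraph: five items, all positively worded; each scored 0 (always present) to 5 (never present); total is the plain sum; a total below 13 is labelled poor well-being.

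**Step 1. Reproduce the stated range.** Minimum 5 × 0 = 0 and maximum 5 × 5 = 25. This matches the article's 0 to 25, so a plain sum of the items as scored is what the text describes.

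**Step 2. Put the two extreme response patterns through the rule as printed.**

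| Response to all five positive items | Total as printed | Below 13? | Label by the cut-off |
|---|---|---|---|
| Always present | 5 × 0 = 0 | yes | poor well-being |
| Never present | 5 × 5 = 25 | no | not poor |

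Both labels are the reverse of what the responses say.

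**Step 3. Relate the two directions.** Reversing an item replaces x by 5 − x. Summed over five items, Σ(5 − x) = 25 − s, where s is the total as printed.

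**Step 4. Check the threshold at every total.** Totals are whole numbers, so s < 13 means s ≤ 12, which is the same as 25 − s ≥ 13. A total below 13 in one direction is therefore always 13 or more in the other. Examples:

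| Total on the scale the cut-off implies | Total as printed (25 minus it) | Below 13 on the implied scale | Below 13 as printed |
|---|---|---|---|
| 3 | 22 | yes | no |
| 7 | 18 | yes | no |
| 12 | 13 | yes | no |
| 13 | 12 | no | yes |
| 18 | 7 | no | yes |
| 22 | 3 | no | yes |

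A check of all 26 totals from 0 to 25 found none classified the same way in both directions.

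**Step 5. Effect on the group comparison.** Let M_EG and M_CG be mean totals as printed. On the reversed scale the difference is (25 − M_EG) − (25 − M_CG) = −(M_EG − M_CG). Subtracting from a constant leaves each group's variance unchanged, so the standard error, the width of the confidence interval and the two-sided p-value stay the same. Only the sign moves. A true gain of 3 points appears as −3.

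**Step 6. Which sentence is out of line?** The cut-off sentence is the only one that interprets the total, and it takes low as poor. The anchor sentence is the only one pointing the other way. Moving the anchors (0 for never, 5 for always) gives 25 to the woman with constant positive feelings and 0 to the woman with none, and the cut-off then labels both sensibly.

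**The case against.** The strongest reply is that the contradiction may exist only in print. The KoBo form is not shown. If it is coded with 5 for constant presence, the data are right and one sentence of the article is wrong. If it is coded as printed and the analyst reads lower as better, the effect is also interpreted correctly. A reversed result needs both things together: coding as printed, and a higher total read as better. The article establishes neither. A reader might infer that the trial will report a reversed well-being effect; the text does not support that.

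A reader might also infer, from the remark that low scorers warrant further assessment, that women who are well would be flagged and women who are not would be missed. The article does not support that either. It makes the threshold neither an endpoint, nor an eligibility rule, nor a referral trigger. Mental health screening rests on the Hopkins checklist, Table 1 does not list the WHO-5 at screening, and the Analysis section describes no dichotomised WHO-5 outcome.

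A third temptation is to settle the direction from the Analysis section's plan "to evaluate the potential increase in the secondary outcomes (well-being". That phrase refers to the construct, not the score. The same set includes the HSCL-25, a distress measure on which a higher score is not a benefit.

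Finally, the error is exactly recoverable, and a WHO-5 result running against the other three well-being measures might prompt a check.

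These replies limit the consequence and the severity. They do not remove the contradiction. Nor is this a detail left to a fuller document: the article chose to state both the anchors and the cut-off, and they disagree.

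**Conclusion.** The point holds as an internal inconsistency in the scoring of one secondary instrument. The anchors and the cut-off cannot both stand without a reversal step, and none is stated.

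The size is conditional. If the form is coded as printed and a higher total is read as better, as the cut-off implies, the EG–CG difference changes sign with its magnitude and p-value intact, and any later use of the threshold is inverted for every participant. If either condition fails, the defect is confined to the published description or to the interpretation of the threshold.

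Family planning use, the sample size and the randomisation are unaffected. Because the reversal is exact, loses no information, and touches one of four well-being measures, this is a should-fix and does not put the trial's main conclusion at risk. The conclusion rests only on the article's own paragraph, with the items taken as positively worded as stated there.

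**What to change.** 1. Correct the anchor sentence so that it agrees with the cut-off: 0 for at no time, 5 for all the time. Add a short statement that a higher total means better well-being.
2. Check the numeric response coding of the WHO-5 items in the KoBo form, at each of T0, T1 and T2.
3. If any data were captured in the direction now printed, recode before analysis: 5 − x for each item, which gives 25 − s for the total.

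The cost is one corrected line, one added statement, a check of five items in the electronic form and, if needed, a simple recode. No further data collection or change to the design is required.

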#### Intermediate outcomes

The intermediate outcomes will measure improvement in important mediators in the EG compared to CG at three months. Mediators include emotional regulation, communication skills, and coping, problem management and decision making.

Emotional regulation will be measured by the Difficulties in Emotion Regulation Scale Short Form (DERS-SF). The DERS-SF consists of 18-items, with participants rating their answers in the past week on a scale from 1 (almost never) to 5 (almost always). Total scores range from 18 to 90, with higher scores indicating more difficulty in emotional regulation (34).

Communication skills will be measured by the Interpersonal Communication Competency Scale (ICCS). The tool assesses ten dimensions of interpersonal communication competence (self-disclosure, empathy, social relaxation, assertiveness, alter-centrism, interaction management, expressiveness, supportiveness, immediacy, and environmental control. A total of 17 questions will be selected from the scale based on a study done in Brazil (32).

Coping, strategies, problem solving, and decision making will be assessed using the Revised Ways of Coping Checklist (RWCCL), which measures different types of coping will also be used. It will enable the research team to evaluate the structure of the interpersonal or individual social supports as well as their collective or networked social supports. The RWCCL is a widely used multidimensional coping measure with satisfactory reliability and validity (33, 36). Specific subscales were chosen based on our aim, and to avoid overlapping questions. The included subscales are: Confrontive coping, Escape-Avoidance, and Planful problem-solving.

### Analysis

A detailed statistical analysis plan will be developed upon completion of the study. The data will first be downloaded from the electronic data collection software, KoBo, and imported into a statistical analysis software.

An Intent-to-treat analysis approach will be adopted to test for significant difference of primary and secondary outcomes over time. For baseline (T0) comparability, descriptive statistics (frequency distributions, means, standard deviations, medians, IQRs) will be obtained for variables collected at baseline outcome evaluation. The Chi-square test and t-test will be used to investigate whether potentially confounding variables are balanced across the two study groups. Any potential bias due to these potential confounders will be evaluated analytically by considering them in the regression model. The internal and external study validity will be evaluated by comparing baseline characteristics of those who completed the study to those lost to follow-up, and by comparing screening characteristics of those included in the study to those eligible but not consented for inclusion in the study.

For primary outcome analysis, binary outcome of FP use (yes/no) will be evaluated between baseline (T0) and endline (T1), and between baseline and 3-month follow-up (T2). To estimate treatment effects, multivariable logistic regression models will be conducted separately for T0-T1 and T0-T2 comparisons to estimate odds ratios of FP use in the intervention group compared to the control group. All models will be adjusted for potential sociodemographic confounders. Given that each model will include one change outcome per participant, within-participant correlation as a result of repeated measures will not arise within individual models.

The primary analysis will be repeated 1- to adjust for potential confounders identified in the bivariate analysis, 2- in the compliant “per protocol” subgroup that attended 6 out of 8 (75%) weekly sessions, 3- to explore the impact of missing data with multiple imputation methods, and 4- to consider the change in FP use from intervention completion to three months.

Analysis of secondary outcomes will be conducted at endline (T1) and 3 months post-intervention (T2) 1- to evaluate the potential increase in the secondary outcomes (well-being), and 2- in the use of the other SRH services associated with the intervention; 3- to investigate potential mediators of the primary comparison; 4- to investigate the effect of co-interventions and adherence. Mediators will be assessed as additional explanatory variables to the primary logistic regression models.

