### Sample size

Sample size calculation was based on a 20% improvement in the primary outcome (use of family planning) in the EG compared to CG at 3 months post intervention (T2). A 30% baseline prevalence of family planning use was assumed in the study population based on observed prevalence of family planning use in humanitarian settings, ranging from 7.1% (in Northern Uganda), 25% (among Afghan female refugees in Pakistan), and 34.5% (among Syrian women refugees in Lebanon) (9, 21–23). Allowing for 30% attrition, a sample size of 380 adolescent girls and young women would provide a 90% statistical power to detect a difference of 20% in family planning use at 3 months (from 30% to 50%) using a two-sided 5% significance level. This is equivalent to a relative risk of 1.67. To ensure external validity of the findings, a purposive sampling strategy will be employed, as the Syrian refugee population is not homogenous in Lebanon. Specifically purposive sampling will be used at the level of the site and community outreach, and not at the level of individual participant. Ultimately, the sample will be randomised from chosen PHCs that were selected to be part of this intervention based on specific criteria discussed in an earlier section.

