### Randomization

Randomization will be conducted after baseline (T0) assessments are completed and will be stratified by site. Eligible participants will be randomly allocated to EG (intervention group) or CG with a 1:1 ratio. Randomization will be conducting using a computer-generated allocation schema, generated by the study statistician. The randomization schema will use permuted block design with sizes of 4, 6, and 8 blocks in a random mixture, so that treatment allocations are equal after each block size. The young women and adolescents will then be informed of their allocation into either the EG or CG over the telephone.

Participants in the EG will be further divided into subgroups of no more than 12 participants per group. These smaller subgroups facilitate better engagement, interaction, and personalized attention, promoting a supportive and comfortable environment for the participants.

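### The primary model names neither site nor baseline family planning use as a covariate, and leaves covariate choice open to baseline significance tests

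*Protocol article*

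**What the plan says.** - Protocol article, Randomization: allocation is 1:1, takes place after the T0 assessment and "will be stratified by site". Study setting gives two primary healthcare centres.
- Protocol article, Table 1: the survey that measures FP use is given to everyone at T0, T1 and T2.
- Protocol article, Analysis, on baseline: "The Chi-square test and t-test will be used to investigate whether potentially confounding variables are balanced across the two study groups". The next sentence says that bias from these variables will be assessed by considering them in the regression model.
- Protocol article, Analysis, on the primary outcome: separate logistic models for T0–T1 and T0–T2 estimate odds ratios of FP use. On covariates it says "All models will be adjusted for potential sociodemographic confounders". It adds that each model holds one change outcome per participant, without defining it.
- Same section: the primary analysis is then repeated, the first time "to adjust for potential confounders identified in the bivariate analysis".
- Same section: the detailed statistical analysis plan is to be written once the study is complete.
- Protocol article, Sample size: "a sample size of 380 adolescent girls and young women would provide a 90% statistical power". The target effect is 30% vs 50% FP use at T2, tested two-sided at 5%, and the total includes an allowance for 30% attrition.

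**The concern.** Three features of the stated analysis need attention.

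1. **Covariates.** Site defines the randomisation and T0 FP use is likely to be a strong predictor of T2 use. Neither is a sociodemographic confounder in the usual sense, so the stated adjustment set does not clearly cover them.
2. **Outcome.** Yes/no at two times gives three values of change (started, no change, stopped). A binary logistic model needs a rule for collapsing these, and none is given. A model of change does not directly yield an odds ratio of FP use.
3. **Selection.** Under sound randomisation, baseline differences between arms are chance. A balance p-value does not show whether a variable predicts FP use, so it is a poor guide to adjustment. As the detailed plan follows study completion, nothing in the article fixes the covariates before outcomes exist.

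At stake are some power, agreement between design and analysis, and confidence that the primary model was not chosen after seeing results.

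**Working it through.** **Inputs from Sample size.** "A 30% baseline prevalence of family planning use was assumed in the study population"; 30% vs 50% at T2; two-sided 5%; 90% power; N = 380; 30% attrition. Randomization gives 1:1.

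**The plan's own figure.**
- Per arm, uncorrected: [1.96·√(2·0.4·0.6) + 1.2816·√(0.3·0.7 + 0.5·0.5)]² / 0.2² = (1.358 + 0.869)² / 0.04 ≈ 124.
- With continuity correction: (124/4)·[1 + √(1 + 4/(124·0.2))]² ≈ 134, or 268 in total.
- Attrition: 268/0.7 = 383, against 380 stated. The figure reproduces.
- Completers: 380·0.7/2 = 133 per arm. Power is 91.9% uncorrected and 89.8% with the correction.

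**Adding T0 FP use.** The protocol gives no T0–T2 correlation, so phi is assumed. With 30% use at T0, control T2 use is 0.3 + 0.7·phi in T0 users and 0.3·(1 − phi) in non-users; at phi 0.5 these are 65% and 15%. A constant log-odds effect is set so that the experimental arm averages 50%. Logistic Wald tests, 133 per arm, 4,000 simulated trials per row:

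| phi | Power, arm only | Power, arm + T0 use | Adjusted only if the T0 balance test is significant | Starting use as outcome |
|---|---|---|---|---|
| 0 | 93.0% | 92.9% | 93.0% | 73.7% |
| 0.3 | 92.4% | 94.0% | 92.8% | 78.0% |
| 0.5 | 92.3% | 96.5% | 93.0% | 86.1% |
| 0.7 | 91.9% | 99.3% | 92.8% | 96.5% |

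A separate simulation at phi of about 0, 0.2, 0.4 and 0.6 gave 92.9% vs 92.8%, 93.3% vs 93.6%, 91.6% vs 95.6% and 91.7% vs 98.5%.

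The fourth column shows that adjusting only after a significant balance test recovers almost none of the gain. The last column is one possible reading of the change outcome: non-user at T0 and user at T2, counted over all participants.

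**Scale.** At phi 0.5 the mean standard error of the log odds ratio rises from 0.258 to 0.309, while the mean odds ratio moves from 2.35 to 3.11. The gain is in power, not in a smaller standard error on that scale. For a risk difference the variance falls by roughly phi², so if the same phi held in both arms, 380·(1 − 0.25) = 285 participants would match 380 unadjusted at phi 0.5.

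**Adding site.** Two equal sites, with assumed control rates:

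| Site rates | Power without / with site | Type I error without / with site |
|---|---|---|
| 25% / 35% | 92.3% / 92.3% | 4.7% / 4.8% |
| 20% / 40% | 93.0% / 93.0% | 4.2% / 4.8% |
| 10% / 50% | 94.8% / 96.1% | 3.0% / 5.2% |

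**Balance tests.** With k independent tests at 5%, the chance of at least one false imbalance is 1 − 0.95^k: 40% for k = 10 and 64% for k = 20.

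**The case against.** - **The primary model has no stated significance rule.** This stands. A reader might infer that it picks covariates by baseline p-values. Selection by bivariate analysis is explicit only for the first repeat, and considering variables in the regression need not mean keeping only the significant ones. Bivariate analysis could also mean association with FP use. The text allows data-driven choice but does not prescribe it for the primary model.
- **Candidates are named in Table 1.** Its confounder row lists sociodemographic factors, family planning and other knowledge, obstetric history, gender disadvantage and domestic violence. That narrows the field, but it is not a model specification and does not mention site.
- **Baseline use is not ignored.** It does enter through the change outcome. But that outcome is undefined, and under the reading simulated above it has less power than T2 use adjusted for T0 use.
- **An adjusted primary model followed by an adjusted repeat can be coherent**, if the repeat adds further variables. This is ambiguity, not contradiction.
- **Covariate lists belong in the analysis plan.** Usually so. Here the article itself states an adjustment set and a role for balance tests, and dates the detailed plan after completion.
- **The numbers are modest.** This stands. In these simulations the arm-only model already exceeds 90% power. The comparison is with an arm-only T2 model, not with the protocol's sociodemographic model, so the gain over the actual plan is not estimated. Adjusting on the balance test did not inflate overall type I error (4.1% to 5.2%).

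**Conclusion.** The point holds as a should-fix on specification. The stated adjustment set names neither the stratum nor T0 FP use, the change outcome is undefined, and covariate choice may be settled after the data are in.

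Adjusting for T0 use is worth about 0 to 7 points of power for assumed phi 0 to 0.7, and about 4 points at 0.4 to 0.5; with no correlation there is no gain. For site the gain is 0 to about 1 point under assumed site rates. The case for including it is consistency with the design.

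The documents do not support three stronger readings: that the sample size is wrong (380 reproduces), that omitting site invalidates the test (it becomes slightly conservative), or that the primary model is stated to select covariates by significance.

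**What to change.** Before outcome data are seen by arm:

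1. Define the primary outcome as FP use (yes/no) at T2 and remove the change-outcome wording.
2. Fit a logistic model on arm, site, T0 FP use and a short named list of covariates measured at T0, whatever the observed balance.
3. For each scale outcome, adjust for site and for that scale's own T0 value.
4. Describe baseline balance without significance tests as a basis for adjustment, and delete the selection by bivariate analysis from the first repeat.
5. Alongside the conditional odds ratio, report a standardised (marginal) risk difference, which matches the 30% vs 50% target in Sample size.

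The cost is wording: site is known, and FP use and the scales are already collected at T0. The small downside is that the adjusted odds ratio is conditional, lies further from 1 than the marginal one and has a larger standard error on the log-odds scale. Item 5 addresses this.
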